# Evaluation of an internet-based aftercare program to improve vocational reintegration after inpatient medical rehabilitation: study protocol for a cluster-randomized controlled trial

**DOI:** 10.1186/1745-6215-14-26

**Published:** 2013-01-25

**Keywords:** Internet-based intervention, Medical rehabilitation, Premature pension, Rehabilitation aftercare, Stress management, Work disability, Work stress

## Abstract

**Background:**

Mental disorders are the main reasons for rising proportions of premature pension in most high-income countries. Although inpatient medical rehabilitation has increasingly targeted work-related stress, there is still a lack of studies on the transfer of work-specific interventions into work contexts. Therefore, we plan to evaluate an online aftercare program aiming to improve vocational reintegration after medical rehabilitation.

**Methods:**

Vocationally strained patients (n = 800) aged between 18 and 59 years with private internet access are recruited in psychosomatic, orthopedic and cardiovascular rehabilitation clinics in Germany. During inpatient rehabilitation, participants in stress management group training are cluster-randomized to the intervention or control group. The intervention group (n = 400) is offered an internet-based aftercare with weekly writing tasks and therapeutic feedback, a patient forum, a self-test and relaxation exercises. The control group (n = 400) obtains regular e-mail reminders with links to publicly accessible information about stress management and coping. Assessments are conducted at the beginning of inpatient rehabilitation, the end of inpatient rehabilitation, the end of aftercare, and 9 months later. The primary outcome is a risk score for premature pension, measured by a screening questionnaire at follow-up. Secondary outcome measures include level of vocational stress, physical and mental health, and work capacity at follow-up.

**Discussion:**

We expect the intervention group to stabilize the improvements achieved during inpatient rehabilitation concerning stress management and coping, resulting in an improved vocational reintegration. The study protocol demonstrates the features of internet-based aftercare in rehabilitation.

**Trial registration:**

International Standard Randomised Controlled Trial Number Register (ISRCTN:ISRCTN33957202)

## Background

Sick leave and premature pension are rising constantly in most high-income countries because of mental disorders [1-3]. Job strain has been proven to be an important determinant for mental and somatic disorders [4,5]. Approximately one third of the patients in medical rehabilitation are reporting significant work-related stress in Germany [6-8]. Therefore, various job-related interventions have been adopted during inpatient treatment to improve vocational reintegration after rehabilitation [9,10]. Whereas the positive effects of job-related interventions on treatment satisfaction and the intention to return to work could be confirmed in short-term analyses [11-15], transfer to patients’ daily work remains to be demonstrated, especially following prolonged work disability [16,17]. New stressors created by rapidly changing tasks, procedures and technologies, and also interpersonal conflicts in the workplace, may lead to a relapse of symptoms and, finally, to an incapacity for work or premature pension. Only by considerable efforts of networking and implementing aftercare programs does the sustainability of treatment effects seem achievable [18,19]. Currently, only a limited number of patients are assumed to have access and to use immediate aftercare following inpatient medical rehabilitation [20]. Sibold and colleagues [21] reported that the most frequently given reasons for non-participation in aftercare programs included incompatibility with duties at work (70.7%), too much time investment (46.5%) and poor access to the outpatient rehabilitation facility (34.1%). Accordingly, travelling time proved to be a significant negative predictor for participation.

Several controlled trials demonstrated the efficacy of internet-based therapy and counseling for various mental disorders [22]. In Germany, 92% of the 30- to 49-year-old age group and 69.1% of the 50- to 59-year-old age group have private web access [23]. The results of Kobelt *et al.*[24] indicate the acceptance of internet-based assessment and diagnostics in inpatient medical rehabilitation. Thus, online interventions are not only more easily accessible for far more patients than outpatient treatment [25] but are also more cost effective [26,27]. Although recent evaluation studies on internet-based aftercare programs after inpatient rehabilitation indicate high patient satisfaction, acceptance and efficacy [28-31], the current percentage of online interventions in rehabilitation amongst all internet-based intervention programs is still very low, with a 9% share [32].

Writing is an important component in most online aftercare programs. Based on Pennebaker’s paradigm [33], the healing effects of expressive writing on both the mental and physical state have been widely accepted [34-38]. Direct feedback by the therapist and by fellow patients presumably has an additional motivating and encouraging function and may also initiate model learning [39]. In a meta-analysis comparing different self-care interventions for chronic disease, Wantland and colleagues [40] found that the participation rate in web-based interventions is higher in interventions that are individually tailored compared with less individual interventions.

To promote the transfer of vocational stress management from inpatient treatment to the work setting, we devised an internet-based aftercare intervention with a weekly expressive writing task, followed by individual feedback from an online therapist within one week day and a moderated patient forum. We compare this individually tailored and therapist-moderated ‘active synchronous intervention’ [41] to a passive (control) intervention by means of an informational website, where patients are regularly alerted by e-mail to publicly accessible information concerning stress management and coping. The online aftercare program extends a manualized vocational stress management group training (Gesundheitstraining Stressbewältigung am Arbeitsplatz; GSA) administered during inpatient rehabilitation through to aftercare. The internet-based aftercare intervention also includes audio samples with relaxation exercises and the GSA worksheets. The efficacy of the GSA training has been demonstrated in short-term analyses for patients treated in psychosomatic, cardiovascular and orthopedic inpatient rehabilitation centers [42], and half of the cooperating clinics have been using parts of the GSA manual since 2006 in their regular stress management programs. With the design of our online aftercare program, we aim to close the gap between inpatient treatment and aftercare and evaluate the acceptance and efficacy of the program across different indications of medical rehabilitation. We expect that participating in online aftercare will lead to a reduced risk of premature pension assessed with a standardized and validated questionnaire.

## Methods

### Participants

Patients are recruited during inpatient psychosomatic, orthopedic or cardiovascular rehabilitation. Eligible patients have to be vocationally strained, assessed by the ‘Screening Instrument zur Messung des Bedarfs an berufsbezogenen Behandlungsangeboten in der medizinischen Rehabilitation’ (Short Screening Instrument for the Assessment of Need for Occupation Related Treatment in Medical Rehabilitation; SIBAR [6]), a short screening questionnaire measuring the social medical risk of early retirement, occupational stress and the subjective need for occupational treatment. Patients are eligible if they report high occupational stress or risk of early retirement appropriate to the cutoff reported by the authors of the SIBAR or if they state a high subjective need for occupational treatment. Furthermore, eligible patients have to be German speaking, currently employed, between 18 and 59 years old and have private internet access, so that they do not have to use internet access at work for participation in our study and are not disturbed by others. Patients are excluded if they are unemployed or retired, or have severe physical or psychological complaints, precluding participation in the stress management training (GSA). We also excluded anyone aged over 59 because the likelihood of retirement is very high over 59 years, limiting therapeutic access to these patients. The Study Centre of Mental Disorders at the University Medical Centre of the Johannes Gutenberg University of Mainz is responsible for storing personal data, encoding the participants and randomizing the groups. Administration of the internet platform, allocation of the weekly writing tasks and therapeutic feedback are managed by psychologists of the Department for Psychosomatic Medicine and Psychotherapy of the University Medial Centre Mainz. The clinical staff of the four rehabilitation centers (one psychosomatic, one orthopedic and two cardiovascular) conducting the inpatient GSA program and introducing the internet-based aftercare to the patients consists of social education workers, psychologists and psychotherapists, all experienced in vocational stress management and psychological group training.

Data security is guaranteed by secure sockets layer-coded internet connections as used in bank transfers and a firewall-protected webserver for both the MySQL-database and the application of the internet platform. All patients are instructed to use pseudonyms to login and for all actions on the internet platform so that no personal data is stored on the webserver; therefore, identification of the user is not possible.

Over a period of 18 months, a total of 800 patients is planned to be included in the study (100 rehabilitants in each center for each randomized arm).

### Interventions

At inpatient admission, patients are informed in detail about the study by the clinical staff of the rehabilitation centers. After giving written consent and screening, the eligible patients are assembled into a group of up to 12 (minimum of two) participants. Over a period of two to three weeks, participants are trained in stress perception and management by four interactive psycho-educative, cognitive-behavioral and psychodynamic modules (90 minutes each). To standardize the procedure, the staff has been trained using a comprehensive manual in a detailed one-day seminar before study start, with a refresher half-way through recruitment. In the first part of the fourth module, the participants are familiarized with the three components of Luborsky’s Core Conflictual Relationship Theme and its recurrent and potentially mal-adaptive nature, focusing on typical expectations regarding return to work [43,44]. This approach also serves as a basis for the upcoming writing task in the intervention group. The introduction to the features of the internet platform, given in the last of four inpatient GSA modules, differs between the two randomized arms. Up to the fourth session, participants and trainers are blind to the result of randomization. Immediately prior to the fourth module, the trainer is unblinded. In the second part of the fourth session, all participants are introduced to the special features of the internet platform. Instructions for participants depend on the arm they are randomized to (intervention versus control). Because there is plenty of interaction between consecutive cohorts of patients admitted to medical rehabilitation, we do not randomize individuals but groups of eligible patients. With this cluster randomization, we aim to minimize contamination through the interaction of patients during inpatient rehabilitation who are getting different instructions for the aftercare interventions in the two randomized arms.

In two of the four rehabilitation centers, patients of both randomized arms have the opportunity to log on to the study website during their inpatient rehabilitation treatment and complete the baseline questionnaire online. In the other two clinics without sufficient technical equipment, the participants get the same questionnaire on a paper-pencil basis and are prepared for their first login at home by the trainer. In any case, every participant gets a sealed envelope including the personal access data and a written description of the intervention or control program. After login, all patients are asked to change their password, to choose a nickname and to enter their e-mail address if they want to be informed by automated e-mails about study-related information, therapeutic tasks and questionnaires to be filled out.

The essential component of the online aftercare program for the intervention group is a standardized weekly writing task (‘blog’) followed by individual feedback from the online therapist within one week day, both only visible to the individual patient and the online therapist. Further online features for the intervention group are a self-test with computer-generated feedback to the participants’ individual ‘Arbeitsbezogenes Verhaltens und Erlebensmuster’, Kurzform 44 (Pattern of Work-related Coping Behavior, short-form 44; AVEM-44 [45]) and its change over time, audio samples with progressive muscle relaxation exercises [46], the GSA worksheets and a moderated patient forum. All these features are accessible for 12 weeks. The internet-based therapeutic interventions are performed by two trained psychologists with regular supervision. With the participants’ consent, all blog contacts between therapist and patient are fully documented in the database, allowing subsequent comparisons and analyses concerning the contents.

The control group receives regular e-mail reminders to use selected and online-deposited information about stress management and coping (physical activity, relaxation, healthy diet and sleep hygiene) over the same period of time. All information is permanently downloadable for participants of the control group for the duration of 12 weeks. Overall there are six e-mail reminders, that is, one every fortnight, beginning with a universal reminder, followed by reminders for the five specific topics on stress management and coping.

### Assessment

As shown in Figure 1, the time points of assessment by self-rating scales are at the beginning (T0) and the end (T1) of inpatient rehabilitation, at the end of the aftercare (T2 = 3 months after T1) and 9 months later (T3 = 12 months after T1). Additional somatic and psychological measures, documented during inpatient rehabilitation, are assessed at T1.

**Figure 1 F1:**
[figure not shown]
**Study design and time points of assessment.**^1) ^patient information, ^2) ^declaration of consent, ^3)^ Screening instrument work and occupation screening, ^4) ^check of inclusion criteria, ^5) ^socio-demographic data, ^6) ^previous treatment, ^7)^ internet use, ^8) ^Arbeitsbezogenes Verhaltens und Erlebensmuster, Kurzform 44 (Pattern of Work-related Coping Behavior, short-form 44), ^9)^ Patient Health Questionnaire, ^10) ^Generalized Anxiety Disorder 7-item Scale, ^11) ^Short-Form 12-item Health Survey, ^12) ^Berlin Social Support Scale, ^13) ^Fragebogen zur Messung der Patientenzufriedenheit (Questionnaire on Patient Satisfaction), ^14) ^inpatient treatment satisfaction, ^15)^ medical discharge report, ^16) ^further treatment, ^17a) ^Helping Alliance Questionnaire (only intervention group), ^18a) ^Helping Alliance Questionnaire II (only intervention group), ^19b) ^frequency of use and satisfaction with website content (different for the intervention and control group).

Depending on the technical equipment in the rehabilitation centers, T1 assessment is conducted online or paper-pencil. All following data are collected internet based, unless the patients do not participate within two weeks. In this case, the patients get paper-pencil questionnaires by mail. The online assessment takes about 45 minutes, comparable to the paper-pencil assessment. Patients get computer-generated feedback following each completed online questionnaire, describing the participants’ individual work-related behavior and experience pattern and its change over time, measured by the AVEM-44 [45]. The feedback is intended to serve as an incentive for participating in the survey.

### Objectives and hypotheses

In this study we evaluate the acceptance and efficacy of an internet-based aftercare program for three different indications of medical rehabilitation (at the participant level), with the following hypotheses:

1. We expect that taking part in the internet-based aftercare program helps stabilize the improvements achieved during inpatient rehabilitation concerning stress management and coping with conflicts at the workplace. Therefore, participants of the intervention will have a lower risk for premature pension than the control group.

2. We expect these effects to persist up to 9 months after the end of the internet-based treatment.

### Outcomes

The primary outcome measure is a risk factor for early pension, measured by the screening questionnaire SIBAR, a score ≤8 indicating a decreased risk for premature pension. The primary endpoint will be the assessment at the end of the internet-based treatment (T2, that is, 3 months after inpatient rehabilitation). Secondary outcome measures include the subjective prognosis for work and capability, also measured by the SIBAR, and scales for the work-related behavior and experience pattern (AVEM-44 [45]), physical and mental health (Patient Health Questionnaire [47], Generalized Anxiety Disorder 7-item Scale [48], Short-Form 12-item Health Survey [49]), social support (Berlin Social Support Scale [50]), therapeutic alliance (Helping Alliance Questionnaire [51], Helping Alliance Questionnaire II [52]) and self-developed items measuring patients‘ satisfaction with the aftercare program. Long-term effects of the primary outcome measure will be analyzed 9 months after termination of the internet-based aftercare at T3. Except for the Helping Alliance Questionnaires, only applied in the intervention group, all instruments are used in both randomized arms.

### Sample size calculation

At present, there are no reports of reliable effect sizes for internet-based interventions aiming at the improvement of vocational strains through online aftercare interventions. We therefore made conservative calculations with an expected small to moderate effect size (d = 0.30), a statistical power of 0.80 and alpha of 0.05. A total sample size of n = 190 will be necessary to gain significant results (calculation with GPower 3.0.10 for analysis of variance with fixed effects, special, main effects and interactions).

Patients are randomized in clusters - the cluster size is set at two to twelve participants. For each clinic, 30 blocks have been generated, each consisting of both groups in random order. Altogether, there is a maximum of 60 clusters per clinic with an equal share of intervention and control groups. To adjust sample size calculation for clustering, we multiplied the needed sample size by the design effect (1+(m-1)ρ, with m = average cluster size and ρ = intracluster correlation coefficient) as suggested in the CONSORT statement extension for cluster randomized trials [53]. With an anticipated average cluster size of six participants and an intracluster correlation coefficient of ρ = 0.30, as reported by Campbell *et al*. for comparable studies [54], we calculated a design effect of 2.5. By multiplying our needed sample size of n = 190 with the design effect we get a minimum sample size of n = 475 needed for robust statistical analyses. Even in case of a dropout rate of 40% as reported in a recent aftercare study [21], the anticipated number of n = 800 (n = 100 per clinic and condition) will provide statistically confirmed data.

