### Statistical methods

For the primary analyses, analysis of covariance will be used to compare SIBAR risk scores 12 weeks after the discharge of inpatient rehabilitation (T2) between the internet-based aftercare program (intervention group) and the control group, with covariates for rehabilitation clinic and baseline SIBAR risk score (T1). Cohen’s effect sizes will be calculated. Intention to treat analyses as well as completer analyses will be conducted. Replacement strategies of missing values will be discussed after assessing the pattern of the missing value structure.

For the secondary analyses, self-report questionnaires (AVEM-44; Patient Health Questionnaire; Generalized Anxiety Disorder 7-item Scale; Short-Form 12-item Health Survey; Berlin Social Support Scale; Helping Alliance Questionnaire) will be analyzed by mixed models with repeated measurements. It is expected that the SIBAR risk score and the other self-report measures will not be linear across time. Therefore, these measures will be evaluated by a linear model with fixed effects for treatment and rehabilitation center and time. There will be an indicator variable for the post treatment measurements and the SIBAR risk score at baseline will serve as a covariate. All analyses will be conducted on a two-sided level of significance of α = 0.05.

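### The base sample size of 190 does not follow from d = 0.30 (about 352 are needed), so power at the stated minimum of 475 is about 54%, not 80%

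*Protocol article*

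**What the plan says.** The Sample size calculation section of the protocol article describes its calculation as conservative and gives the inputs as an "expected small to moderate effect size (d = 0.30), a statistical power of 0.80 and alpha of 0.05". From GPower's fixed-effects analysis of variance routine it concludes: "A total sample size of n = 190 will be necessary to gain significant results". It names neither Cohen's f, nor the numerator degrees of freedom, nor the number of groups.

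It then applies a design effect for an average cluster of six and an intracluster correlation of 0.30, and states: "we get a minimum sample size of n = 475 needed for robust statistical analyses". Allowing for 40% dropout, it says that "the anticipated number of n = 800 (n = 100 per clinic and condition") "will provide statistically confirmed data".

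The Statistical methods section fixes the sidedness: "All analyses will be conducted on a two-sided level of significance of α = 0.05". It defines the primary analysis as an analysis of covariance comparing the two arms at T2, adjusted for clinic and the baseline SIBAR risk score.

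**The concern.** A total of 190 is far too small for a two-group comparison at d = 0.30 with 80% power. It is the only base figure in the section. The clustered minimum of 475 and the assurance about 800 are both derived from it.

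If it is wrong, the trial has no valid statement of its power. A reader who trusts the printed 80% could take a non-significant primary result as good evidence that a small-to-moderate effect is absent. On the stated inputs, such an effect would be missed almost half the time.

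**Working it through.** **Inputs.** From Sample size calculation: d = 0.30, power 0.80, alpha 0.05, 1:1 allocation, average cluster m = 6, intracluster correlation 0.30, dropout 40%. From Statistical methods: two-sided alpha, two-arm contrast.

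**1. The protocol's later steps reproduce.**
- Design effect: 1 + (6 − 1) × 0.30 = 2.5
- Clustered n: 190 × 2.5 = 475
- Recruitment: 475 / 0.6 = 792, rounded up to 800; and 800 × 0.6 = 480 completers

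**2. The base figure does not reproduce.**
- Normal approximation, per arm: 2 × (1.960 + 0.842)² / 0.30² = 174.4, so 175 per arm and 350 in total.
- Exact noncentral t: 176 per arm, 352 in total.
- Noncentral F, the calculation behind an ANOVA routine: for two equal groups f = d/2 = 0.15. With 1 numerator df the total is 351.

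**3. Other readings that were tried.**

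| Reading | Total n |
|---|---|
| d = 0.30, one-sided (exact t) | 278 |
| f = 0.15, 2 df | 432 |
| f = 0.15, 10 df | 731 |
| 0.30 entered as f, 1 df | 90 |
| 0.30 entered as f, 7 df | 167 |
| 0.30 entered as f, 10 df | 190 |

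No variant that treats 0.30 as d gives 190. Only the last row matches (with 2, 4 or 8 groups). It would mean that d was entered as f, and f = 0.30 corresponds to d = 0.60 for two equal groups. It would also mean testing a 10-df effect and not the 1-df arm contrast. This is a possible source inferred from matching numbers; the article does not state it.

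**4. The same chain with the right base.**
- 352 × 2.5 = 880 analysable
- 880 / 0.6 = 1,467 recruited

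**5. Power for d = 0.30 at the planned size.** The noncentrality is d√N/2, with N the effective sample size.
- 475 analysed: N = 475 / 2.5 = 190; 0.30 × √190 / 2 = 2.07; power 53.9% (exact t).
- 480 analysed: N = 192; power 54.3%.
- All 800 analysed, no dropout: N = 320; power 76%.
- Effect detectable with 80% power at N = 190: 2 × 2.802 / √190 = 0.41.

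**6. Sensitivity to assumptions the article does not make.** Here r is the baseline–outcome correlation, and adjustment multiplies the required n by 1 − r².
- Design effect 2.5, 475 analysed: power is about 58% at r = 0.3, 67% at r = 0.5, 73% at r = 0.6 and 83% at r = 0.7.
- Correlation at which 190 would be right: √(1 − 190/352) = 0.68.
- Clusters thinned by dropout to 6 × 0.6 = 3.6: design effect 1 + 2.6 × 0.30 = 1.78; effective N = 480 / 1.78 = 269.7; power 69% unadjusted, with d = 0.34 detectable at 80% power.
- Thinned clusters and r = 0.5 together: power about 81%.

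**The case against.** The best defence is that 54% is not the power of the analysis actually planned. The primary model adjusts for baseline SIBAR score and clinic, which gains precision. Dropout of 40% would also probably shrink the analysed clusters, so that a design effect of 2.5 overstates the loss. With clusters of 3.6 and r = 0.5, the requirement is 352 × 0.75 × 1.78 = 470 analysable, or 783 recruited, which is within 800. With clusters of 3.6, 480 completers reach 80% power at r of about 0.48. On this view 880 and 1,467 are an upper scenario.

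This stands as a limit on the conclusion: the trial's true power cannot be fixed from the article, and it may be adequate. It does not rescue the printed calculation. The article describes a plain ANOVA, gives no correlation, and itself applies 2.5 to the analysed patients, so 880 and 1,467 follow its own method.

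It is also fair to say that the mix-up of d and f is unproven. Two arms by four clinics make eight cells and so at most 7 df between cells, which leaves a 10-df effect without an obvious origin. The error does not depend on the explanation. Nor does condensation into a journal article excuse it, because the inputs and the result are both printed and disagree.

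**Conclusion.** The concern holds. For the stated d, power and alpha, the unclustered total is 351 to 352; the printed 190 is 54% of that. The figures of 475 and 800 inherit the error. On the protocol's own design effect, power for d = 0.30 is about 54% at 475 to 480 analysed patients, and 80% power is reached only at d of about 0.41.

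The 54% assumes no gain from baseline adjustment and a design effect of 2.5 among those analysed. Smaller clusters alone give 69%; an assumed r = 0.5 alone gives 67%; the two together give about 81%. Those are assumptions added here. As written, the calculation is not conservative and does not support the assurance attached to 800.

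**What to change.** Correct the Sample size calculation section in one of two ways.

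1. Keep the present method. Give 352 as the unclustered n and 880 as the clustered n for d = 0.30. State that 480 completers provide about 54% power for d = 0.30, and 80% power for d of about 0.41, at an intracluster correlation of 0.30 and clusters of six.
2. Preferably, base the calculation on the planned ANCOVA. State and justify a baseline–outcome correlation and the average cluster size expected among analysed patients, then quote the resulting power for 480 completers.

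In either case, state the numerator degrees of freedom and the effect-size measure used. Remove the description of the calculation as conservative and the claim that 800 "will provide statistically confirmed data".

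The cost is a text correction and, under the first option, a less favourable stated power. Enrolment began in July 2011, and no additional recruitment is requested.

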### Randomization

With the help of the computer software Research Randomizer [55], a block randomization has been conducted by the Study Centre of Mental Disorders. Stratified according to the four clinics to achieve an equal share of intervention and control groups, the lists have been assigned to the trial sites by a researcher not involved in the study.

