With the cluster randomization, patients are enrolled in the study as cohorts and therefore we are confident that they are more motivated to take part and less likely to drop out of the study than in an individually randomized design. With the, for the most part, blinded inpatient training we try to enable that both intervention group and control group are treated the same during inpatient rehabilitation. Unfortunately, a completely blinded assessment of the outcome was not possible, because patients needed to be informed about the group and intervention they are randomized to, during inpatient rehabilitation. However, our main outcome is assessed by study participants, independent from the online therapist. The fact that the intervention group and control group use the same medium after inpatient rehabilitation for the follow-up assessments will help us to reduce possible confounding factors when interpreting the results of the comparative analyses. Overall, and from a practical point of view, we think that not only because of the close connection between the design of our online aftercare program and the inpatient GSA training during rehabilitation but also because of the interdisciplinary approach, combining cognitive, behavioral and psychodynamic elements in training and aftercare, our internet-based aftercare program could be a very promising supplement for inpatient rehabilitation.

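### Fixed blocks of two groups per clinic let the second group's arm be deduced once the first is revealed, so trainer blinding in modules 1 to 3 is not assured for up to half of the groups

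*Protocol article*

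**What the plan says.** Sample size calculation (protocol article) describes the lists: "For each clinic, 30 blocks have been generated, each consisting of both groups in random order". It continues: "Altogether, there is a maximum of 60 clusters per clinic with an equal share of intervention and control groups". Randomization adds that the scheme is run separately by site, "Stratified according to the four clinics to achieve an equal share of intervention and control groups", and that "the lists have been assigned to the trial sites by a researcher not involved in the study".

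Interventions makes the blinding claim: "Up to the fourth session, participants and trainers are blind to the result of randomization". It then sets the moment of disclosure: "Immediately prior to the fourth module, the trainer is unblinded". The Discussion leans on this to argue that the arms had equal inpatient care: "With the, for the most part, blinded inpatient training we try to enable that both intervention group and control group are treated the same".

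On enrolment, Interventions says: "At inpatient admission, patients are informed in detail about the study by the clinical staff of the rehabilitation centers". Groups of 2 to 12 are formed after consent and screening. The training is also delivered by clinical staff of the centers (Participants). The article does not say whether sites knew the block length.

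**The concern.** In a block of two, the second allocation is fixed by the first. The first group's arm becomes known on site before its fourth module, while the next group may be in training or still being formed. A list held by someone outside the study does not prevent this, because the next arm follows from the last one. Nor does staff knowledge depend on being told. Under this scheme no arm can occur three times running in a clinic, and a trainer who sees the arms in turn could notice that.

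Two protections are affected, to different degrees:

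- **Trainer blinding in modules 1 to 3.** This is claimed explicitly and used to argue that both arms were treated alike before the aftercare began.
- **Concealment while a group is being filled.** Group size is flexible, and exclusion for severe complaints needs judgement, so foreknowledge could influence who joins.

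The outcome is self-reported by patients who know their arm, so protection before allocation carries more weight than it would with blinded assessment.

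**Working it through.** **Inputs.** 30 blocks and at most 60 clusters per clinic, average cluster size 6 (Sample size calculation). Four clinics, 800 patients, hence 200 per clinic, over 18 months (Participants). A course of two to three weeks with four modules (Interventions).

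**1. Block size.** 60 / 30 = 2. The plan's maximum of 60 is reproduced only with blocks of two.

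**2. Predictability, if the pairing is known and the first arm has been revealed.** The first group is guessed correctly with probability 0.5, the second with probability 1. Share of groups fully determined: 1/2. Average correct-guess rate: (0.5 + 1)/2 = 0.75. Simulation of 3,000 lists of 60 gave the same 0.50 and 0.75. If the first arm has not yet been revealed, the values are 0 and 0.50, so timing decides how much is exposed.

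**3. Number of groups.** Maximum: 4 × 60 = 240, of which 120 are second in a block. At the planned size: 800 / 6 = 133, of which 133 / 2 ≈ 67 are second.

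**4. Timing.** 18 months = 78 weeks, and 200 / 6 = 33.3 groups per clinic. Interval between starts: 78 / 33.3 = 2.34 weeks, or 78 / 60 = 1.3 weeks at the maximum number of clusters. Assumptions, not stated in the article: evenly spaced starts, module 4 at the end of the course, and each group filled in the interval before its start.

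| Interval (weeks) | Course (weeks) | First group's reveal, relative to second group's start | Part of second group's course after the reveal | Part of second group's recruitment after the reveal |
|---|---|---|---|---|
| 2.34 | 2 | 0.34 weeks before | all | 0.34/2.34 = 15% |
| 2.34 | 3 | 0.66 weeks after | 2.34/3 = 78% | none |
| 1.3 | 2 | 0.7 weeks after | 1.3/2 = 65% | none |
| 1.3 | 3 | 1.7 weeks after | 1.3/3 = 43% | none |

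On these assumptions the reveal always precedes the second group's own fourth module, but little or none of its recruitment follows the reveal. Wider spacing changes the second result. With every group at the upper limit of 12, the interval is 78 / (200/12) = 4.68 weeks, and the share of recruitment after the reveal is 1.68/4.68 = 36% (3-week course) to 2.68/4.68 = 57% (2-week course). There would then be only 800/12/2 ≈ 33 second groups.

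**5. Comparison.** With fixed blocks of known length, the share of fully determined groups falls from 50% (blocks of 2) to 33% (blocks of 4) and 25% (blocks of 6). The correct-guess rate falls from 75% to 71% and 68%. Longer blocks alone therefore help only moderately. Varying the length and not disclosing it reduces certainty further.

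**The case against.** A reader might infer that every second group's arm was known in advance, so that concealment failed for half the clusters and about 400 of 800 patients were recruited into a known arm. The article does not support this, for four reasons.

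- **Deducible is not disclosed.** The Study Centre randomizes and an uninvolved researcher assigned the lists. Whether the block length was withheld is a detail that an article may leave to the full protocol.
- **The persons may differ.** Only the trainer is unblinded. Nothing shows that whoever recruits or trains the second group is the trainer who learned the first group's arm.
- **Recruitment mostly comes first.** Consent and screening precede the group's start. At the planned pace most second-group enrolment would be over before the reveal.
- **Concealment is not expressly claimed.** The explicit claim is blinding of participants and trainers, and this mechanism does not directly unblind participants.

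The article also hedges. The Discussion calls the training blinded only for the most part and admits that trainer bias cannot be wholly prevented. Delivery is manualized, with a training seminar and a refresher, and the primary analysis of covariance adjusts for SIBAR at T1.

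These arguments limit the reach of the point but do not remove it. The hedges do not mention the pairing. T1 is the end of inpatient rehabilitation, after any unequal training, so adjusting for it deals at best with differences visible in the SIBAR score. The timing that protects recruitment also places much of the second group's first three modules after the reveal.

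**Conclusion.** The point holds as a limit on what the design guarantees. Blocks of two with disclosure before each fourth module mean that trainer blinding in modules 1 to 3 is not assured for up to half of the groups: about 67 of 133 at the planned size, 120 of 240 at the maximum. The figure is a ceiling. It assumes that staff know or infer the pairing and that the first arm reaches the second group's trainer in time. Different trainers, poor communication between them or overlapping courses all lower it.

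Concealment at recruitment is a narrower risk, confined to second groups still being filled after the first group's reveal. Under even spacing this is roughly 0 to 15% of a second group's recruitment period, and more where groups start further apart. The first group in each block stays unpredictable. The article gives no evidence that bias occurred.

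**What to change.** **Any group not yet allocated.** Replace the remaining list by permuted blocks of randomly mixed size within clinic (for example 4 and 6 groups). Do not disclose the sizes to sites, and have the Study Centre release one arm at a time just before module 4. The cost is new lists and possibly a slight imbalance in group numbers per clinic.

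This probably comes too late. Trial status puts the last follow-up in September 2013, and T3 is 12 months after T1, so the last T1 falls at about September 2012. A full 18 months from 1 July 2011 would run to the end of December 2012. Both precede publication on 25 January 2013.

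**Groups already allocated.**

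1. Qualify the blinding statements in Interventions and the Discussion: trainers were not told the arm before module 4, but it could be deduced for the second group of each pair. State whether sites knew the block length and whether consecutive groups shared a trainer.
2. Compare group size and SIBAR at T0 by arm and block position. T0 is the right baseline here because it precedes the training.
3. Add a sensitivity analysis of the treatment effect by block position (first = unpredictable, second = deducible), allowing for the group as the randomized unit.

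The cost is a few sentences and one additional analysis of data already held. Each position contains about half the groups, so with similar group sizes its standard error is about √2 ≈ 1.4 times that of the whole-trial estimate. Report the two estimates with intervals, and do not read similar estimates as proof that no bias arose.
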